## Abstract

**Background:**

Acupuncture has been used in China to treat tinnitus for a long time. There is debate as to whether or not *De Qi* is a key factor in achieving the efficacy of acupuncture. However, there is no sufficient evidence obtained from randomized controlled trials to confirm the role of *De Qi* in the treatment of acupuncture for tinnitus. This study aims to identify the effect of *De Qi* for patients who receive acupuncture to alleviate tinnitus by a prospective, double-blind, randomized, sham-controlled trial.

**Methods and design:**

This study compares two acupuncture groups (with or without manipulation) in 292 patients with a history of subjective tinnitus. The trial will be conducted in the Teaching Hospital of Chengdu University of Traditional Chinese Medicine. In the study, the patients will be randomly assigned into two groups according to a computer-generated randomization list and assessed prior to treatment. Then, they will receive 5 daily sessions of 30 minutes each time for 4 consecutive weeks and undergo a 12-week follow-up phase. The administration of acupuncture follows the guidelines for clinical research on acupuncture (WHO Regional Publication, Western Pacific Series Number 15, 1995), and is performed double-blind by physicians well-trained in acupuncture. The measures of outcome include the subjective symptoms scores and quantitative sensations of *De Qi* evaluated by Visual Analog Scales (VAS) and the Chinese version of the ‘modified’ Massachusetts General Hospital Acupuncture Sensation Scale (C-MMASS). Furthermore, adverse events are recorded and analyzed. If any subjects are withdrawn from the trial, intention-to-treat analysis (ITT) and per-protocol (PP) analysis will be performed.

**Discussion:**

The key features of this trial include the randomization procedures, large sample and the standardized protocol to evaluate *De Qi* qualitatively and quantitatively in the treatment of acupuncture for tinnitus. The trial will be the first study with a high evidence level in China to assess the efficacy of *De Qi* in the treatment of tinnitus in a randomized, double-blind, sham-controlled manner.

**Trial registration:**

Chinese Clinical Trial Registry: ChiCTR-TRC-14004720 (6 May 2014).

## Background

Tinnitus is a spontaneous, internally generated noise, which can be heard in the ear or in the head. The prevalence of tinnitus is estimated among 8 to 30% [1] and the exact causes of it remain unknown. Malfunction of the auditory end-organ, which could be caused by any condition, might cause subjective tinnitus, but the commonest cause is age-related degeneration. Other causes include Meniere’s disease, trauma (acoustic or chemical), and cardiovascular diseases. The reasons for the onset of tinnitus of each individual are still unclear and this may explain why different treatments of the disease are beneficial for some patients but not for others [2]. Patients with tinnitus complain bitterly about the persistent noise and impairments of quality of life and work are common, particularly in patients with moderate/severe tinnitus.

Different treatment methods have been tried to alleviate tinnitus, which include sound therapy (masking) [3], repetitive transcranial magnetic stimulation therapy [4], cognitive behavioral therapy, tinnitus retraining therapy and pharmacological treatment (antidepressants, anxiolytics and night sedatives). Although there are so many treatment options for tinnitus patients these methods are not universally effective due to its unclear etiology and pathogenesis. Also because levels of evidence of most of the trials to treat tinnitus are generally limited, the efficacy of most interventions for tinnitus benefit remains to be demonstrated conclusively [5].

As a result, complementary or alternative therapies, such as acupuncture, are attractive to both patients and practitioners. In China, acupuncture has been used for alleviating tinnitus since ancient times. Some studies aiming to evaluate the therapeutic effects of acupuncture on the neurogenic tinnitus indicate that acupuncture can improve tinnitus in some selected patients [6]. There is also a theory stating that acupuncture may influence the function of the olivocochlear nucleus [7]. In order to achieve the best therapeutic effect from acupuncture, *De Qi* is emphasized in traditional Chinese theory [8]. Describing the compound word ‘*De Qi*’ separately, *De* means ‘obtain’ and *Qi* indicates the most primitive substance in the universe that remains in constant motion. In general, the term means a stimulation that reaches a threshold that elicits nerve impulse transmission to the cerebral cortex. In vivid description, *De Qi* describes an acupuncture needle sensation of soreness, tingling, fullness, aching, cool, warmth and heaviness, and a radiating sensation at and around the acupoints. *De Qi* has been explained to some degree to be in closely correlated with the intensity of the stimulus, so it plays a pivotal role in achieving the best therapeutic effects [9–14]. Although the concept of *De Qi* is a long-held belief that ensures the efficacy of acupuncture for tinnitus, it has not been confirmed qualitatively and quantitatively by sufficient evidence from randomized controlled trials. Additionally, without the feeling of *De Qi*, the therapeutic effect of acupuncture for tinnitus may be compromised. Thus, we designed a randomized, double-blind clinical trial to compare the efficacy of acupuncture with either strong (intended to elicit *De Qi*) or weak stimulation among patients with subjective tinnitus. The design and methodologies of this study have been approved by Sichuan Regional Ethics Review Committee on Traditional Chinese Medicine with an ethics approval number of 2014KL-006. The work reported in this article is registered with an identifier (ChiCTR-TRC-14004720) by the Chinese Clinical Trial Registry.

## Methods and design

### Study design

This is a prospective, double-blind, randomized and sham-controlled trial that compares two acupuncture groups (with or without manipulation). This study protocol has been approved by Sichuan Regional Ethics Review Committee on Traditional Chinese Medicine (project number: 2014KL-006). Also, the trial reported in this article is registered by the Chinese Clinical Trial Registry with an identifier of ChiCTR-TRC-14004720. The trial will be performed according to the principles of the Declaration of Helsinki (Version Edinburgh 2000). In addition, written informed consents will be taken from all patients.

### Population

The study population will be recruited at the Teaching Hospital of Chengdu University of Traditional Chinese Medicine (TCM), China. A total of 292 patients, aged 18 to 60, who complain of subjective tinnitus, will be initially enrolled in our study. The total study period will be 17 to 18 weeks, which includes the following time points: a run-in period of 1 week after screening, a treatment period of 4 weeks and a follow-up period of 12 weeks (Figure 1). The trial is to be executed from January 2014 to December 2014.

**Figure 1 Fig1:**
[figure not shown]
**Tools used for outcome measurement: Visual Analog Scale (VAS), Tinnitus Handicap Inventory (THI), Tinnitus Severity Index Questionnaire, Tinnitus Loudness Questionnaire, and 10-cm VAS C-MMSAA: Chinese version of the ‘modified’ Massachusetts General Hospital Acupuncture Sensation Scale (C-MMASS).** A flowchart of the procedure of this clinical trial.

### Inclusion criteria

Patients who will be recruited in this study should meet the inclusion criteria including:Present with subjective tinnitus, unilateral or bilateralBe aged between 18 and 60 years oldNot be participating any other clinical trialsHave no previous acupuncture experienceProvide a written informed consent and accept the treatment schedule.

### Exclusion criteria

Patients with any of the following conditions will be excluded:Those with objective tinnitusThose whose history, physical examination and imaging studies reveal any structural etiology for their complaint, such as acoustic tumor, head trauma, and cerebral vascular eventsPregnant women or women who are expecting to be pregnant in the recent half year, or lactating womenThose who are unwilling to cooperate.

### Withdrawal from the study

The study patients will be allowed or be asked to withdraw from the study if:They would prefer not to be subjected to the assigned treatment for various reasons at any of the trial stagesSevere adverse events occur that necessitate their withdraw from the trialThey cannot fully participate in the treatment or follow-up.

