### Measurements of tinnitus

The efficacy of acupuncture treatment for tinnitus is assessed in terms of the severity and loudness of tinnitus. Tinnitus Handicap Inventory (THI) and a 10-cm Visual Analog Scale (VAS) are used. Patients complete the THI and VAS before the treatment and every four weeks during the following period. The 25-item THI consists of three scales: a functional subscale, a catastrophic response subscale and an emotional subscale. Before and after the acupuncture treatment, the participants are asked to report their tinnitus on the THI Questionnaire with ‘Yes’ (4 points), ‘Sometimes’ (2 points) or ‘No’ (0 points). Based on the total THI score, each patient’s tinnitus severity could be categorized into ‘no handicap’ (0 to 16), ‘mild handicap’ (18 to 36), ‘moderate handicap’ (38 to 56) and ‘severe handicap’ (58 to 100).

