### Quality control

All acupuncturists are required to receive special training, including the technique for puncture and the way to deal with adverse events. The acupuncturists should also learn how to use the randomization method in order to communicate with patients and to keep them blind to the treatment throughout the trial. Only those who have completed the required training and have passed all necessary examinations will be recruited for this trial. In order to maintain quality of this trial, all outcome assessments will be blinded. In addition, all researchers must understand the purpose and design of this trial. Audits will be conducted regularly on compliance with standard operation procedures every week. Report of audits should be presented to the chief monitor. If patients withdraw from the trial either in the treatment period or in the follow-up phase, the reason should be clarified and the rate should be statistically analyzed.

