### Statistical analysis

We conducted a pilot study, in which the similar outcome measurements were used, to determine the sample size prospectively. In this pilot study, the two methods of manipulation and non-manipulation were about 70 and 50% effective respectively when the patients underwent acupuncture 5 times a week for 4 weeks. Based on the population rates of the two groups, the following formula is used to estimate sample size [16]:

Calculations are performed c 5% significance level. In the formula, α = 0.05, Z_0.05_  = 1.96, β = 0.10, Z_0.10_  = 1.282; n_1_, n_2_ represents the sample size of each group respectively and π_1_ = 0.50, π_2_ = 0.70, π_c_ = (π_1_ + π_2_)/2 = 0.60. Thus as a result, an estimated 146 patients per group should be recruited when allowing for a 15% withdrawal rate.

Statistical analysis will be performed using the statistical software package SPSS 19.0 for windows (SPSS Inc, Chicago, IL, USA). Firstly, the baseline characteristics of the two groups, such as age, weight, duration of tinnitus, THI and VAS scores, will be analyzed by an unpaired *t*-test or paired t tests. Then, the second step is to compare the efficacy of *De Qi* or not in the treatment of tinnitus. The average intensity of *De Qi*, the total number of *De Qi* acupoints of all the treatment sessions, the scores of THI and VAS will be tested for normal distribution. If the data follow normal distribution, a two-sample (independent) *t*-test will be used. The data that are not conforming to the normal distribution will undergo Wilcoxon testing. A level of *P*-value less than 0.05 will be considered statistically significant.

Furthermore, the intention-to-treat analysis (ITT) and per-protocol (PP) analysis should be conducted as two principles to test whether the result of this trial is credible. Any cause of withdrawal or loss to follow-up should be clarified. Qualified statisticians will perform the statistical analysis in a blinded manner.

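### The withdrawal rule does not separate stopping treatment from leaving the study, so it can lose THI and VAS outcomes that the promised intention-to-treat analysis needs

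*Protocol article*

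**What the plan says.** The section Withdrawal from the study opens: "The study patients will be allowed or be asked to withdraw from the study if". Three grounds follow: the patient would rather not have the assigned treatment, at any stage; a severe adverse event makes withdrawal necessary; or the patient "cannot fully participate in the treatment or follow-up". In each case the patient leaves the study, and the section has no separate category for stopping treatment only.

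On outcomes, Measurements of tinnitus says: "Patients complete the THI and VAS before the treatment and every four weeks during the following period". Population gives "a treatment period of 4 weeks and a follow-up period of 12 weeks", so the schedule runs to week 16.

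On analysis, the Abstract says: "If any subjects are withdrawn from the trial, intention-to-treat analysis (ITT) and per-protocol (PP) analysis will be performed". Statistical analysis says that ITT and PP "should be conducted as two principles to test whether the result of this trial is credible".

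On patients who leave, Quality control asks that "the reason should be clarified and the rate should be statistically analyzed", and Statistical analysis again asks for the cause. Neither section mentions collecting outcomes after withdrawal.

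**The concern.** An ITT comparison needs outcomes from patients who did not complete their assigned treatment. The withdrawal section lets or asks those same patients to leave. Treatment is 20 sessions over four weeks. Read literally, someone who misses a few sessions has not fully participated and may be asked to go, even if willing to keep filling in questionnaires.

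Two things are at stake. First, outcomes may be missing for reasons linked to treatment and prognosis, which can bias the comparison of randomised groups. Second, the plan uses ITT and PP side by side as a check on credibility. The more the ITT analysis lacks data from patients who stopped, the closer it comes to the PP analysis, and the less their agreement shows.

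This is a rule about data collection, not a detail that can wait for the analysis plan. A later plan can choose how to handle missing scores, but it cannot recover scores that were never collected. The article's own Discussion criticises earlier tinnitus trials for exclusion and attrition bias.

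**Working it through.** **Step 1. Set the sections side by side.**

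| Question | Where | What it gives |
|---|---|---|
| Who may leave or be asked to leave? | Withdrawal from the study | Includes patients declining assigned treatment and those not fully participating |
| What do they leave? | Withdrawal from the study | The study |
| Are THI and VAS continued afterwards? | No section | Not stated |
| What is recorded for them? | Quality control; Statistical analysis | Reason (both) and withdrawal rate (Quality control) |
| Who must the analysis include? | Abstract; Statistical analysis | ITT, beside PP |

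Scores are taken before treatment and then every four weeks. A patient who leaves within the first four weeks may therefore have no post-baseline score. A patient who leaves later loses only the remaining assessments.

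**Step 2. Reproduce the plan's sample size.** Inputs from Statistical analysis: π₁ = 0.50, π₂ = 0.70, π_c = 0.60, z values 1.96 and 1.282, withdrawal 15%. The printed formula is not in the text at hand; the usual pooled form gives

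n = [1.96·√(2·0.60·0.40) + 1.282·√(0.50·0.50 + 0.70·0.30)]² / 0.20² = 124.04, or 124 per arm.

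124.04 / 0.85 = 145.9, so 146 per arm and 292 in total, as stated. The plan thus allows for 0.15 × 146 = 21.9, about 22 withdrawals per arm (44 in all). With 124 completers per arm, power is 90.0%. The allowance protects the number of completers; it does nothing about bias.

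**Step 3. Bound the all-randomised difference.** Assume that all 15% in each arm lack outcomes and that completers show 70% versus 50%.

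- Lower bound (no missing manipulation patient responds, every missing non-manipulation patient does): 0.85·0.70 = 0.595 versus 0.85·0.50 + 0.15 = 0.575; difference 2 points.
- Upper bound (the reverse): 0.595 + 0.15 = 0.745 versus 0.425; difference 32 points.

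**Step 4. A less extreme illustration, with assumed inputs.** Suppose no true effect: 50% respond in each arm. Let d be the share withdrawing and q the response among withdrawers. The completer rate is (0.50 − d·q)/(1 − d). The type I error is for a two-sided 5% test of two proportions in the completers of 146 per arm.

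| Withdrawal, arm A v arm B | q | Completer rates, A v B | Spurious difference | Type I error |
|---|---|---|---|---|
| 10% v 20% | 30% | 52.2% v 55.0% | 2.8 points | about 7% |
| 10% v 20% | 0% | 55.6% v 62.5% | 6.9 points | about 20% |
| 15% v 15% | 30% | 53.5% v 53.5% | 0 | 5% |

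The last row matters: equal withdrawal with equal prognosis gives no bias here.

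**Step 5. What full follow-up does to power.** With all 146 per arm followed and 70% versus 50% undiluted, power is 94.1%. If 15% of the manipulation arm stop and then respond at 50% (an assumption), that arm's rate is 0.85·0.70 + 0.15·0.50 = 0.67, and power is about 84%.

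**The case against.** The strongest reply is that the text is permissive and condensed. Patients are allowed or asked to leave; the article does not say that everyone who misses a session is removed, or that scores already collected are discarded. A fuller protocol may settle what happens after discontinuation. The plan also gives attrition some attention, through reasons and an analysis of the rate.

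Much of this stands, and it rules out several stronger readings that a reader might infer:

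- *Removal is compulsory.* The wording does not say so. The defect is that the rule permits or requests departure and makes no provision for continued assessment.
- *ITT is done only if someone withdraws.* The Abstract is phrased conditionally, but Statistical analysis says without condition that "the intention-to-treat analysis (ITT) and per-protocol (PP) analysis should be conducted as two principles". With 15% withdrawal allowed for, the condition has little practical effect anyway.
- *ITT and PP must agree by construction.* They need not. A patient who leaves during follow-up can contribute earlier scores to ITT while being excluded from PP, and PP may drop patients with deviations who have complete scores.
- *The named tests force a completers-only analysis.* A t-test or Wilcoxon test can follow imputation. How missing scores are handled can be left to the analysis plan.
- *Strong needling will drive dropout in one arm.* The arms differ by design in needle sensation, so this is plausible, but the article gives no withdrawal by arm, and patients are blinded to method.
- *The 2 to 32 points are the expected damage.* They are the limits for any trial with 15% missing per arm and these completer rates. Some of the 44 would be lost under any rule. The bounds also use the response rates of the sample size calculation, whereas the planned tests compare scores.

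What does not stand is that the matter can be left to the analysis plan. The article states the rule, the rule governs which data exist, and it works against the analysis that the same article promises.

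**Conclusion.** The concern holds in a limited form. The withdrawal section treats stopping treatment and leaving the study as one event, and no section keeps outcome collection going. Followed as written, it can lose later THI and VAS scores from patients whom ITT must include and weaken the ITT and PP comparison as a check.

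The sample size itself is sound. The exposure is up to about 22 patients per arm, if the whole 15% allowance lacks outcomes. The share of these who would leave only because they stopped or missed treatment is not given, so the part that the rule itself causes cannot be sized. Whether bias follows, and in which direction, depends on withdrawal or prognosis differing by arm; that is an assumption.

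**What to change.** In Withdrawal from the study, separate the two events. State that patients who stop or miss sessions, for whatever reason, keep all scheduled THI and VAS assessments to week 16 unless they withdraw consent to follow-up. Remove incomplete participation as a ground for being asked to leave the study. In Statistical analysis, and to match in the Abstract, state that all randomised patients are analysed as randomised, with PP as supportive. The method for scores that are still missing can be set in the analysis plan.

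The grounds for stopping treatment itself are unchanged and are not judged here.

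The cost is protocol wording and some follow-up for questionnaires that patients complete themselves. Including patients who stopped may dilute the observed effect, as in Step 5, but that is the comparison ITT is meant to make. The change should be in place before patients start to leave, because lost outcomes cannot be recovered.

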### Recruitment and randomization procedures

The participants will be recruited through advertisements in local newspapers, hospital websites, and television. Printed recruitment posters will also be posted in the hospital and the university campus. Then, the participants will be randomly assigned to either the manipulation or the non-manipulation group with an assignment ratio of 1:1 according to the random number of allocation sequence generated by computer (using SPSS 19.0 statistical software package, IBM, Chicago, IL, USA). The random allocation numbers are sealed separately in opaque envelopes separately. After the participants have picked-up one of the envelopes, their random numbers and corresponding randomization information, such as the participant’s name in a pinyin format and gender, will be recorded in a random allocation table in duplicate and sealed in an opaque container respectively. The container will not be opened until blinding has ceased. A well-trained acupuncture practitioner, who has practiced for more than ten years, performs the intervention according to the assignment. Also, the acupuncturist does not participate in any of the subsequent evaluation phases. Investigators, including the study physicians and the analyzing statistician, are blinded to the manipulation group assignment.

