### Acupuncture administration

All candidates go through a standardized interview and undergo a temporal bone computed tomography (CT) scan, audiological testing of hearing thresholds, minimal masking levels, and loudness discomfort levels. Participants will also be asked to complete the Tinnitus Severity Index Questionnaire (a standard questionnaire with 13 items for quality of life in patients suffering tinnitus), Tinnitus Loudness Questionnaire, the Hospital Anxiety and Depression Scale (HANDS) at the screening visit and at 4, 8 and 16 weeks after randomization. The patients in both the manipulation group and the non-manipulation group are blinded as to which treatment method they would receive. For both groups, treatment consists of five daily sessions of thirty minutes each time for four consecutive weeks.

Acupuncture will be performed by an acupuncturist who has more than ten years experience and has obtained an acupuncture license (Chinese medicine practitioner license), which is licensed by the Ministry of Health of the People’s Republic of China). In order to make the patients comfortable and relaxed during treatment, a constant humidity and a temperature of 20 to 25°C is necessary. Subjects will be advised to assume a supine position on the bed. As has been mentioned above, three basic points and three to four secondary acupoints are selected for each patient according to syndrome differentiation. When the acupoint sites have been located and disinfected with 75% alcohol cotton, a sterile disposable stainless needle of 0.3 mm diameter and 25 mm in length (Suzhou Hualun Medical Appliance Co., Ltd, Jiangsu, China) is inserted gently into the SI19, GB2, SJ21, PC8 and LR3 points separately for a depth of about 0.25 to 0.5 *cun*. For ST40, GB40, BL26 and KI13, a needle with the diameter of 0.3 mm and a length of 40 mm is used with the approximate puncture depth of 0.5 to 1 *cun*. It is advisable to retain the needles for 10 to 20 minutes for the subtypes of deficiency of Kidney-*yin*, while this is not necessary for the other two subtypes with excess syndromes. For the whole treatment, the insertion and withdrawal of the needle is at a constant speed.

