For the manipulation group, patients are to be acupunctured with some genuine manipulations by lifting, thrusting, and twirling the needle to generate needle sensation, known as *De Qi* (described above). When *De Qi* occurs, the internal compound sensation of soreness, numbness, distension, dull pain, coldness, warmth, heaviness, and radiation at and around puncture points may be felt. Also, the acupuncturists may also feel the sensation of sinking, stagnancy, tightness and astringency. In non-manipulation group, the acupuncturist inserts the needles without using any acupuncture techniques. Patients receive one treatment session daily for five consecutive days, and the total treatment course lasts for four weeks.

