### Assessment of acupuncture sensation ‘*De Qi*’

The Chinese version of the ‘modified’ Massachusetts General Hospital Acupuncture Sensation Scale (C-MMASS) is used to record the patients’ sensations of *De Qi* quantitatively. The C-MMASS was established on the basis of MASS. In C-MMAS, the terms have been translated into precise Chinese, but one description, ‘sharp pain’, was removed from the scale. The validity and reliability of the scale have been examined by exploratory study [15]. The descriptor in C-MMASS includes soreness, aching, deep pressure, heaviness, fullness/distension, tingling, numbness, dull pain, warmth, cold, throbbing, and there is one supplementary row at the end for subjects to describe perceptions in their own words. Each of the elements is presented on a 10-cm bar to indicate the degree of needle sensation from ‘none’, ‘mild’, ‘moderate’ to ‘severe’. Subjects are asked to quantify their sensations at each acupoint immediately after each treatment by rating their intensities on the numerical bar. If the participants have any sensations not given in the scale, they could describe them at the end of the scale. Then, for each subject, the total *De Qi* scores of the 20 sessions will be calculated together for final statistical analysis.

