## Discussion

Although acupuncture is one of the major parts of TCM, it is regarded as a useful complementary therapy to conventional medicine and the efficacy of acupuncture has been proven by many randomized controlled trials [17–19]. Also, it has been widely believed that the needle sensation is important in acupuncture treatment. In one of our surveys of acupuncture treatment for tinnitus, most of the patients and acupuncturists believed that stronger needle sensations led to better treatment results. However, it is still believed by some researchers that the therapeutic effects of acupuncture are due to the psychological factors [20]. The relationship between *De Qi* and treatment effects is still controversial. Further studies were conducted to explore the relationship among *De Qi*, psychological factors, and clinical efficacy. Xiong *et al*. [21] reported that it was *De Qi*, but not psychological factors, that determined the therapeutic efficacy of acupuncture treatment for primary dysmenorrhea. Kong *et al*. [22] found significant correlations between analgesia and needle sensations of numbness and soreness on experimental pain, which suggested that attributes of *De Qi* sensations might be useful clinical indicators of effective treatment. As for tinnitus, although there was pilot, sham-controlled and double-blind trial to verify the efficacy of the treatment of acupuncture [18], the degree and the type of *De Qi* were not clarified. Further study should be designed to explore the relationship between *De Qi* and acupuncture points, stimulation and treatment effects.

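### Recruiting in a TCM hospital and on what is evidently a TCM campus, without excluding people trained in acupuncture or TCM, weakens patient blinding of self-rated outcomes

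*Protocol article*

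**What the plan says.** **Where patients come from.** The Population section states: "The study population will be recruited at the Teaching Hospital of Chengdu University of Traditional Chinese Medicine (TCM), China". Recruitment and randomization procedures lists local newspapers, hospital websites and television, and adds: "Printed recruitment posters will also be posted in the hospital and the university campus".

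**Who is eligible.** The inclusion criteria require that a patient has had no acupuncture before and give no reason for the rule. The four exclusion criteria cover objective tinnitus, structural causes, pregnancy or lactation, and unwillingness to cooperate. Neither list mentions training or employment in acupuncture or TCM.

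**What is blinded and how the arms differ.** Acupuncture administration states: "The patients in both the manipulation group and the non-manipulation group are blinded as to which treatment method they would receive". In the manipulation arm the needle is lifted, thrust and twirled to produce a felt sensation. For the other arm: "In non-manipulation group, the acupuncturist inserts the needles without using any acupuncture techniques".

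**Who rates the outcomes.** On the tinnitus measures: "Patients complete the THI and VAS before the treatment and every four weeks during the following period". On the needle sensation (C-MMASS): "Subjects are asked to quantify their sensations at each acupoint immediately after each treatment by rating their intensities on the numerical bar".

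**What patients expect.** The Discussion reports from the authors' own survey that "most of the patients and acupuncturists believed that stronger needle sensations led to better treatment results".

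**The concern.** The treatment difference can be felt by the patient. Blinding therefore relies on patients not knowing what the presence or absence of the sensation means. The eligibility rule tests whether a person has been needled, which is not the same as whether that person has been taught what De Qi is. A TCM student, nurse or other employee with tinnitus who has never been needled meets the criteria as written, and posters in the hospital and on the campus reach exactly these people.

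If some of them work out their arm, their ratings may follow their expectation. Blinded assessors and a blinded statistician give no protection, because the patient makes the rating. The Discussion treats psychological factors as the disputed rival explanation for acupuncture's effects. An expectation bias would point the same way as the hypothesis and could be read as an effect of De Qi.

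**Working it through.** **1. Does the gap in eligibility exist?** Set the sections side by side. The Population section names one university, a TCM university. Recruitment and randomization procedures refers to the university campus without naming it, so reading it as that TCM campus is an inference, though a natural one. The inclusion list screens for experience, and no item on either list screens for training. The gap exists as written.

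**2. The plan's own sample size.** Inputs from Statistical analysis: "α = 0.05, Z_0.05_ = 1.96", Z for β = 0.10 of 1.282, π₁ = 0.50, π₂ = 0.70, π_c = 0.60, and 15% withdrawal.

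- n = [1.96·√(2·0.60·0.40) + 1.282·√(0.50·0.50 + 0.70·0.30)]² / 0.20² = 124.04, about 124 per group
- 124 / (1 − 0.15) = 145.9, so 146 per group and 292 in total

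The stated figure reproduces, and this point does not affect it. The number analysed is about 124 per group (146 × 0.85), or 127 if the 15% was added on (146 / 1.15).

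**3. How large could the bias be?** The document gives neither the share of patients who would recognise their arm nor the strength of any expectation effect. Both are assumed here and varied. The response scale is used because it is the only one for which the article gives figures.

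Assumptions: no true effect; 60% response in both arms (the plan's π_c); a share f of each arm recognises its allocation; among these, the response rate differs by b between arms in favour of manipulation.

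- Spurious difference: d = f·b, giving rates of 0.60 + d/2 and 0.60 − d/2
- Chance of a significant result favouring manipulation: Φ[(d − 1.96·SE₀) / SE₁]
- SE₀ = √(2·0.60·0.40/n), with SE₁ the unpooled standard error at the shifted rates

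One case in full, for n = 124, f = 0.20, b = 0.20: d = 0.04, SE₀ = 0.0622, SE₁ = 0.0622. Then (0.04 − 0.1220)/0.0622 = −1.32, and Φ(−1.32) = 0.094.

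| f | b | d | n = 124 | n = 127 |
|---|---|---|---|---|
| 5% | 10 points | 0.5 points | 3.0% | 3.0% |
| 10% | 20 points | 2 points | 5.1% | 5.1% |
| 20% | 20 points | 4 points | 9.4% | 9.5% |
| 30% | 20 points | 6 points | 15.9% | 16.2% |

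The nominal value in that direction is 2.5%. A gap of 20 points among recognisers equals the whole design difference (70% against 50%), so the last three rows are not mild assumptions.

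**The case against.** **The people in question are inferred.** The article mentions no TCM students or staff, and campus posters are one channel among several. If the campus is a minor source, shares of 20% or 30% may be well above reality. This stands. It is why the range has to start at a negligible effect.

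**There are safeguards.** Quality control requires acupuncturists to be trained to keep patients blind throughout. The experience rule also removes any student or employee who has been needled. Both arms receive real needle insertion at points chosen by the same scheme, and a person never needled has no earlier sensation to compare with. All of this is fair. It reduces the risk but does not close the gap, since training the acupuncturist cannot remove what the patient already knows.

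**The expectation is not confined to the campus.** By the Discussion, most surveyed patients already link stronger sensation with better results, and every patient rates needle sensation after each session. This stands too: the proposed exclusion removes the best-informed patients, not the expectation.

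**This is operational detail.** Interview questions may well sit in a fuller protocol. But the article itself sets out the eligibility lists and the poster sites, and it is their combination that leaves the gap.

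**Stronger readings to resist.** A reader might infer that the experience rule was written to stop patients recognising their arm and that campus recruitment defeats it. The article gives no purpose for the rule, and nothing in it shows that blinding fails. A reader might also reach false-positive rates of about 10%, 25% and 50% for shares of 10%, 20% and 30%, by moving response 20 points up in one arm and 20 down in the other. The arithmetic is right, but it implies a 40-point gap among recognisers, twice the design difference, and nothing in the article supports that.

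**Conclusion.** The point holds in a limited form. Recruitment in a TCM hospital and on what is evidently a TCM campus, with no exclusion for acupuncture or TCM training, admits people who may recognise their arm in a trial whose efficacy and sensation measures are all self-rated. That is an avoidable weakness in patient blinding, not a demonstrated failure of it.

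The size cannot be established from the article. Across the assumed range, the chance of a false positive favouring manipulation runs from about 3% (negligible against 2.5%) to about 16%. It depends entirely on the assumed share of recognisers and the assumed gap among them. The sample size is unaffected.

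**What to change.** Add one exclusion criterion: current or past students, practitioners or employees in acupuncture or TCM. Apply it by one question at the standardized interview that every candidate already undergoes. Because it acts on the person and not on the poster site, it also catches trained people who arrive through newspapers, websites or television.

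The cost is one line of eligibility text, one question, and the loss of a minor recruitment source. The change does not remove expectation bias among the remaining patients. If the exclusion is not wanted, a weaker alternative is to record such training and the recruitment source for a sensitivity analysis. Asking patients to guess their arm would help to judge the blinding in either case.
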